### Exclusion criteria

The patient is permanently in an inpatient facility (for example palliative care or a hospice) for a terminal condition.The patient has a severe comorbidity whose treatment takes priority.The patient is in a disease management program.The patient is pregnant or breastfeeding.

### Measuring instruments and variables

The variables recorded in the study and the instruments used for that purpose are explained below:

#### Number of hospitalizations (primary endpoint)

This information is obtained by surveying the patients and also provided by the participating centers (medical controlling). Hospitalization is defined as a hospital stay which includes at least one overnight stay any time after the start of the study.

#### Psychological stress (secondary endpoint)

The Hospital Anxiety and Depression Scale (HADS) is validated for somatic diseases, for example, cancers of all indications, stages, and treatments [14, 15]. The instrument measures the patient’s psychological stress (anxiety and depression) during the previous week. It consists of 14 questions, each with four response categories. 0–3 points are awarded per response, and the sum score is calculated for each patient. A score of less than seven points means an unsuspicious result, a score of 8–10 points a suspicious result, and a score of over ten points a highly suspicious result. The scale is available in a validated German version [16]. The test has an internal consistency (Cronbach’s alpha) of 0.80, a test-retest reliability of *r* > 0.80 and good convergent and discriminant validity.

#### Quality of life of patients

The 36 items in Short Form 36 (SF-36) provide a validated cross-disease (generic) measurement tool for assessing the health-related quality of life of patients, which is also used in routine clinical practice [17]. The questionnaire captures eight dimensions of subjective health: Physical functioning, Physical role function, Physical pain, General health perception, Vitality, Social functioning, Emotional role function and Mental well-being; they can be assigned to the basic dimensions of physical and mental health. With a single item, the current state of health is also inquired compared to last year [18].

#### Question concerning subjective health perception

This validated instrument measures patients’ general subjective health status with just one question [19, 20], with five response options being given: 1 = “very good”, 2 = “good”, 3 = “moderate”, 4 = “poor”, 5 = “very poor”. A higher value indicates poorer health. The instrument is recommended by the World Health Organization and is also used in large-scale studies such as the European Health Interview Survey (EHIS).

#### Quality of life of relatives

This is being represented by subjective health perception questionnaire and HADS.

#### Social support/resources

The MOS Social Support Survey (SSS) is a short questionnaire for patients with chronic diseases [21]. Patients are asked to answer 19 questions describing four areas: emotional/informal support, measurable support, subjective support, and positive social interaction. There are five response options to each question. A cumulative score (social support index) is then calculated. For all areas, Cronbach’s alpha is > 0.91. The questionnaire has a high degree of convergent and discriminant validity.

#### Health literacy of patients

The HLS-EU 16 is the short version of the 47-question European Health Literacy Survey Tool [22, 23]. It covers the areas of knowledge, motivation, competency in gaining access to health services, and the ability to understand and appreciate information pertaining to healthcare, the prevention diseases, and the promotion of health. There are five response options for each of the 16 questions. A cumulative score is obtained for each patient which is classified into one of three categories: insufficient health literacy (range 0–8), problematic health literacy (9–12), and sufficient health literacy (13–16). Cronbach’s alpha for the score is 0.88.

#### Patient activity

The Patient Activation Measure (physicians’ version of PAM-13) allows a patient’s self-evaluation to be assessed [24]. Each of 13 questions has five response options (from 1 = “I strongly disagree” to 4 = “I strongly agree” and 5 = not applicable). Responses are converted to a score ranging from 0 to 100, with low scores indicating a low degree of patient activity. Cronbach’s alpha for the score is 0.80.

#### Joint decision-making

The questionnaire on participatory decision-making for chronic diseases (PEF-FB) consists of nine questions, each of which is answered on a six-point scale [25]. For each physician, the mean is calculated and converted into a standardized participation value ranging from 0 to 100 (with higher values indicating better participation). Cronbach’s alpha for the questionnaire is 0.88.

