#### Other secondary and explorative target parameters

Other target parameters will be compared between the intervention group and the control group. They include:The patients’ quality of lifeThe relatives’ quality of lifeThe psychological burden on relativesHealth status / general sense of healthSocial support / resources of patientsThe patients’ health literacyJoint decision-making between the patient and physicianDays absent from workThe waiting time for required treatmentsCompliance with treatmentsDouble testsSatisfaction with the treatmentsWorkflows / operational processesUse of servicesHealthcare costs

In addition, explorative analyses are planned, including analyses of the type of cancer and other patient-relevant variables.

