## Methods/design

In line with the primary study objective, the design was chosen so that evidence of the effectiveness of the intervention can be generated at the highest possible level of evidence. The project was therefore designed as a prospective randomized, longitudinal, multicenter study. To our knowledge, no other RCT has been conducted in Germany on this topic. Other groups used a quasi-experimental design in which the control group was generated from insurance data [11]. A multicenter approach was chosen to obtain larger sample sizes and to ensure that the study optimally represents cancer centers. In addition, various types of cancer will be considered to assess the effectiveness of the program across multiple indications.

The program was implemented at five centers in Saxony, Germany. The evaluation also takes into account the network partners (office-based physicians) of the specialized hospitals, insofar as they contribute patients to the program.

Eligible patients are identified during their hospitalization in the participating centers and are informed about the study in a personal interview and with the help of written documents. If the patients give their written consent, they are randomized to the intervention group or the control group on a one-to-one basis. They are randomized with regard to the center, the type of cancer, gender, and age group. The following cancers are documented: pancreatic, gastric, colonic/rectal carcinoma, gynecological cancer and melanoma. While patients in the control group receive standard care, those in the intervention group are also in regular contact with their patient navigator.

The observation period in the intervention (cancer patient navigation program participation) and control (no cancer patient navigation program participation) groups is 12 months per patient. In this time period about 20 talks with the cancer patient navigation program specialists shall be held.

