### Study population

The study population comprises cancer patients who have been hospitalized at least once at one of the centers participating in the study as well as their relatives, outpatient and inpatient physicians, and cancer patient navigation program specialists. The inclusion and exclusion criteria for participation in the study must be observed.

Relatives of patients may be included regardless of their degree of relatedness, provided that they are of legal age and have declared their written consent to participate in the study. However, patients should nominate a close family member. Inclusion criteria for hospital physicians are that they must be employed at the hospital and have completed a good clinical practice course. Office-based physicians must be network partners of one of the participating hospitals. Participating cancer patient navigation program specialists must have successfully completed the SKG “Onkolotse” training course, have worked for at least two years in nursing at a cancer unit, and have cared for at least ten patients in their capacity as nurse navigation specialist prior to the study.

Neither the participating physicians nor the cancer patient navigation program specialists may have familiar relationships with the participating patients.

At least 340 cancer patients will be included in the study. The aim is to include not more than one family member per patient, although the exact number is not specified. Nor are the numbers of hospital-based and office-based physicians defined in advance.

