#### Statistical methods

The data are analyzed using SAS Version 9.4 (SAS Institute Inc., Cary, NY, USA). In general, the data analyses focus on the differences between the intervention group and the control group at baseline and the other data-collection times in the study. An error probability of alpha = 0.05 is defined as the significance level.

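### Joint decision-making is scored as one mean per physician, a unit that does not fit a comparison between arms of individually randomized patients

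*Protocol article*

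**What the plan says.** The Joint decision-making subsection of the protocol article describes an instrument that "consists of nine questions, each of which is answered on a six-point scale". It then fixes the scoring: "For each physician, the mean is calculated and converted into a standardized participation value ranging from 0 to 100".

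Four other places in the article bear on this rule:

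- **Unit of randomization.** Under Methods/design, consenting patients are allocated individually: "they are randomized to the intervention group or the control group on a one-to-one basis". The factors are listed: "They are randomized with regard to the center, the type of cancer, gender, and age group". Physician is not one of them, and no section assigns physicians to an arm.
- **Intended comparison.** The section on other secondary and explorative target parameters says: "Other target parameters will be compared between the intervention group and the control group". Joint decision-making is on the list that follows.
- **Number of physicians.** The Study population section leaves this open: "Nor are the numbers of hospital-based and office-based physicians defined in advance".
- **Scoring of other instruments.** The HADS sum score and the HLS-EU 16 cumulative score are each defined per patient. The PEF-FB is the instrument for which the article names the physician as the unit.

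**The concern.** The unit of scoring (physician) is neither the unit of randomization nor the unit of the planned comparison (patient). Because allocation is per patient and ignores the physician, one physician can treat patients of both arms. A single value for that physician belongs to neither arm.

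An analyst who follows the sentence as written has two options. One is to analyse one value per physician, in which case no arm contrast can be formed for physicians with patients in both arms. The other is to give every patient the mean of his or her physician, in which case each patient's value is diluted by the other patients' answers, whatever their arm. Either could hide a real effect on an outcome close to one of the program's stated aims, the active part the patient takes in treatment.

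**Working it through.** **The plan's own figure.** The article gives no figure for this outcome. Its only sample size concerns the primary endpoint, and it reproduces. With p1 = 0.25, p2 = 0.125, alpha 5% (two-sided assumed) and power 80%:

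n = [1.960 × √(2 × 0.1875 × 0.8125) + 0.842 × √(0.1875 + 0.1094)]² / 0.125² = 151.9, so 152 per group, as stated. With 10% dropout, 152 / 0.9 = 168.9, so 169, against 170 stated. None of this depends on the PEF-FB.

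**Is a physician with patients in both arms likely?** "The program was implemented at five centers in Saxony, Germany". With 340 patients, that is 340 / 5 = 68 per center on average. If 10 physicians per center took part (an assumption), each would have 6.8 trial patients. Under simple 1:1 allocation the chance that a physician with m patients has both arms is 1 − 2 × 0.5^m: 50% at m = 2, 75% at m = 3, 94% at m = 5 and 98% at m = 7.

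**Effect of assigning the pooled mean to each patient.** Let the true arm difference be δ. A patient's own answer makes up 1/m of the physician's mean. Under simple allocation the other m − 1 patients have, in expectation, the same arm mix whichever arm this patient is in. The expected difference between arms is therefore δ/m. It does not depend on the standard deviation or on the correlation within physician.

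**Check by simulation.** Inputs: 306 evaluable patients (340 × 0.9), spread evenly over J physicians; assumed δ = 10 points, SD 20, intraclass correlation 0.05; 3,000 runs per setting.

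| J (assumed) | m = 306/J | 1/m | Retained, simple allocation | Retained, arms balanced within physician |
|---|---|---|---|---|
| 5 | 61.2 | 1.6% | 1.5% | 0.0% |
| 10 | 30.6 | 3.3% | 2.9% | 0.1% |
| 20 | 15.3 | 6.5% | 6.0% | 0.3% |
| 30 | 10.2 | 9.8% | 9.2% | 0.2% |
| 50 | 6.1 | 16.3% | 16.0% | 0.3% |
| 100 | 3.1 | 32.7% | 32.6% | 10.1% |
| 306 | 1.0 | 100% | 99.9% | 100.3% |

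The simulated shares follow 1/m. With patient-level scoring the same runs recovered 9.94 to 10.08 of the 10 points. The last column shows that dilution is stronger still if the arms happen to be balanced within each physician.

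**The case against.** The strongest reply is that the article never says that answers are averaged over patients of both arms. The sentence stands in a description of instruments and may mean something else:

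- the mean of the nine items on each questionnaire, reported for the physician whom it concerns;
- the nine-item mean for the physician as respondent, since the article does not say who completes the PEF-FB (this keeps the contrast only if the physician completes one form per patient);
- a physician mean formed separately within each arm.

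The stated aim of comparing the groups favors a reading that permits the comparison. The detailed analysis of such outcomes may also sit in the statistical analysis plan, to which the article refers.

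Much of this stands. Pooling over arms is the literal reading, not a stated one, and the 1/m result needs the further step that each patient is given the physician's mean, which the article does not describe. A reader might infer that the trial will average its two arms together and that the effect on joint decision-making will nearly vanish. The document does not support that as a flat statement: the pooling is not written, and with the number of physicians left open the loss could lie anywhere from none to almost all.

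The reply does not rescue the wording. If the nine-item mean per questionnaire was meant, the sentence names the wrong unit, while the article names the patient for the HADS and the HLS-EU 16. If a mean within arm was meant, the text has to say so. Nor is this a detail merely left to the analysis plan: the article fixes a unit, and that unit does not fit the design.

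**Conclusion.** The point holds as a defect in the definition of one outcome. As written, the PEF-FB score has no arm label for any physician with trial patients in both arms, and so cannot serve the comparison that the article plans.

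The size is conditional. It assumes that the physician mean pools both arms, that each patient is then given that mean, and a value of m that the article does not supply. On those assumptions about 1/m of the true difference is retained: everything at m = 1, which could apply to office-based physicians with a single trial patient, and very little for hospital physicians with many.

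The consequence is limited. Joint decision-making is one of a long list of other secondary and explorative outcomes. The primary endpoint, the HADS endpoint and the sample size are untouched, and the item answers allow rescoring.

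**What to change.** In the Joint decision-making subsection, replace the per-physician mean by one value per patient questionnaire and time point: the mean of the nine items on that questionnaire, converted to 0-100. State that these values are compared between the randomized arms. Keep any physician-level mean as a description of physicians only. Whether to allow for clustering by physician or center can be left to the statistical analysis plan.

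The cost is about one sentence, with matching wording in the analysis plan. The item data stay the same, and no further patients are needed.

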#### Days of work missed

The number of days from the start of the study on which the patient was unable to work − as confirmed by a medical certificate − is recorded. The details of the patients are documented on a specially created questionnaire.

#### Waiting time for required treatment

The waiting time is measured in days and is based on information provided by the patients themselves.

#### Compliance with treatment

Information on the patient’s compliance with the treatment is recorded by the physician on a standardized questionnaire. In cases where treatment is stopped, the causes are documented.

#### Doublication of tests

The medical controlling and network partners provide information on this subject on standardized questionnaires. Imaging and other diagnostic procedures are included.

#### Satisfaction with the intervention

The satisfaction of patients, physicians and relatives with the intervention program is recorded in questionnaires on a 5-point Likert scale (from “strongly agree” to “strongly disagree”).

#### Workflow/operative processes

Information on time spent with the patient, perceived time saving, improvements in physician-patient communication, and subjective evaluation of the effectiveness of the intervention is solicited in questionnaires and rated on a five-point Likert scale (from “strongly agree” to “strongly disagree”).

#### Medical treatment

Physicians are asked in questionnaires to provide information about their patient’s medication. This includes immunotherapy, cancer-specific therapy, chemotherapy with the aim of improving survival and response rates, and established palliative treatment and best supportive care to improve symptoms and quality of life.

#### Utilization of healthcare services

Patients are asked on the questionnaire to what extent they have utilized such services. They include rehabilitation, physiotherapy, psycho-oncological treatment, physician contacts with and without referral, care by the family physician, admission to an emergency room or hospital, duration and reason for hospitalization.

#### Disease costs

The costs of diagnostic and therapeutic measures are obtained from the participating centers (medical controlling). If they are not available in full, secondary data, for example hospital statistics, will be used.

#### Covariables

The physician questionnaire records information on the type and stage of the cancer pursuant to the UICC TNM classification. In addition to patient questionnaires, demographic information is collected on, inter alia, age, gender, educational attainment, living conditions, work situation, migration background, work incapacity, and relationship status. Finally, patients are asked about any comorbidities based on a list of conditions.

### Statistics

#### Sample size planning

The sample size planning is based on the primary endpoint, whose one-year incidence is estimated to be 25% in 2015 and 2016 according to data from the participating study centers. Based on earlier study findings, the case management program can halve the number of hospitalizations [11].

Thus, a hospitalization rate of 12.5% is expected in the intervention group. To illustrate this difference at a significance level of alpha = 5% and a statistical power of 80%, 152 patients per group are needed (chi^2^ test, normal approximation, PROC POWER SAS 9.4). Taking into account a dropout rate of 10% during the 12-month study period, a total of 170 patients per group, or 340 patients in total, are needed at baseline.

#### Statistical methods

The data are analyzed using SAS Version 9.4 (SAS Institute Inc., Cary, NY, USA). In general, the data analyses focus on the differences between the intervention group and the control group at baseline and the other data-collection times in the study. An error probability of alpha = 0.05 is defined as the significance level.

#### Descriptive data analysis

Appropriate descriptive statistical methods are applied depending on the scales used for the individual variables. Categorical variables (for example, the hospitalization rate) are expressed as absolute and relative distributions. In the case of continuous data, the following parameters are calculated: frequency, number of missing values, mean with standard deviation, minimum, maximum, median, and 25 and 75% quartiles. Suitable graphic methods are used for visualizing the data, e.g. box plots.

#### Primary endpoint

As a starting point, the hospitalization rates, defined as the percentage of patients who spend at least one night in hospital during the one-year study period in the two groups, are compared by means of the chi^2^ test. The results are verified in a second analytical step using a general linear model that takes into account other influencing factors.

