### Program description

“Onkolotse” cancer patient navigation program specialists are trained, SKG-certified nurses/carers, professionals, counselors, psychologists or social workers working in the field of oncology [13]. They are extensively trained in special self-paid courses that are divided into seven modules and comprise over 130 h of tuition. Training topics include issues relevant to cancer patients, in particular structures, processes, and contact persons in the management of the disease. The “Onkolotse” cancer patient navigator program stands for trustworthy information, support, and advice rooted in understanding and care, as well as psychological issues relating to cancer treatment [13]. Patients and their family members are assigned a skilled, permanent contact person to whom they can address their questions during the entire duration of cross-sectoral treatment and who also has the necessary time to devote to them. Care does not end with the acute phase of the disease but continues throughout rehabilitation and aftercare. Topics of the consultation can be, for example: which hospitals provide interventions or rehabilitation measures, what support services are available from authorities or health insurance funds (e.g. severe disability status, aids, rehabilitation), and who is able to provide outpatient aftercare. The knowledge gain, the support in developing or maintaining a positive attitude, and the teaching of problem-solving skills increase the individual’s health literacy and enable active, independent participation of the patient in the treatment process. Overall, continued support can help patients and relatives to cope better with a cancerous disease and to feel more at ease within the healthcare system.

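### The chi-square test and the 80% power treat patients as independent although intervention patients share navigators; if navigators differ in effect, power is overstated and the p-value is too small for transfer to other navigators

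*Protocol article*

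**What the plan says.** All references are to the protocol article.

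- **Allocation (Methods/design).** Individual patients consent and then "they are randomized to the intervention group or the control group on a one-to-one basis". Center, cancer type, gender and age group are named as randomization factors.
- **Intervention.** Program description: "Patients and their family members are assigned a skilled, permanent contact person". Methods/design: controls receive standard care, while "those in the intervention group are also in regular contact with their patient navigator". About 20 talks are planned per patient over 12 months, at five centers.
- **Sample size planning.** The control rate is the endpoint "whose one-year incidence is estimated to be 25% in 2015 and 2016", and "a hospitalization rate of 12.5% is expected in the intervention group". At 5% alpha and 80% power, "152 patients per group are needed" by a chi-square calculation. The only inflation is for 10% dropout, giving 170 per group and 340 in total.
- **Primary endpoint.** The proportions with at least one night in hospital "are compared by means of the chi^2^ test". A second-step model then verifies the result, with covariates that are not named.
- **Secondary endpoint.** HADS is compared by a t test.
- **Aim (Objectives and hypotheses).** The results are meant to help decision-makers transfer the program to routine care.

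No number of navigators, caseload, ICC or design effect is given.

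**The concern.** This is an individually randomized trial with clustering in one arm (a partially nested design). Study population requires navigators to have the society's training, two years in cancer nursing and at least ten earlier patients. With five centers and 170 intervention patients, it is reasonable to infer that several patients share one navigator, although the article does not say so.

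If some navigators prevent more admissions than others, outcomes of patients with the same navigator are correlated. The intervention-arm rate then varies more than the binomial formula allows. The chi-square test, the t test for HADS and the 152-per-group calculation all leave this variation out.

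Two things are at stake. The chance of detecting the planned difference may be below 80%. And a result driven by a few good or poor navigators could be read as a property of the program. That matters because transfer to routine care means other navigators.

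**Working it through.** **1. The plan's own figure.** Inputs from Sample size planning: p1 = 0.25, p2 = 0.125, alpha 5%, power 80%. Sidedness is not stated; two-sided reproduces the figure.

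Mean rate = 0.1875, so pooled variance = 0.1875 × 0.8125 = 0.15234.

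n = [1.960 × √(2 × 0.15234) + 0.8416 × √(0.25 × 0.75 + 0.125 × 0.875)]² / 0.125² = (1.0819 + 0.4586)² / 0.015625 = 151.9, so 152 per group. Power at 152 is 80.03%. For dropout, 152 / 0.9 = 168.9, so 169 (stated as 170). The arithmetic is sound under independence.

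**2. Adding navigators in one arm.** Assumed inputs: J navigators with equal caseload m = 152/J, and an ICC. Design effect in the intervention arm: DE = 1 + (m − 1) × ICC; in the control arm it is 1.

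- SE under the null = √[0.15234 × (1 + DE) / 152]
- SE under the alternative = √[(0.1875 + 0.109375 × DE) / 152]
- Power = Φ[(0.125 − 1.960 × SE null) / SE alternative]

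*J = 10, ICC 0.02:* m = 15.2, DE = 1 + 14.2 × 0.02 = 1.284. The SEs are 0.04785 and 0.04645. Power = Φ[(0.125 − 0.09377) / 0.04645] = Φ(0.672) = 74.9%.

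*J = 5, ICC 0.05:* m = 30.4, DE = 1 + 29.4 × 0.05 = 2.47. The SEs are 0.05897 and 0.05487. Power = Φ[(0.125 − 0.11559) / 0.05487] = Φ(0.172) = 56.8%.

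Power of a test that allows for navigators, at 152 per group:

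| Navigators (patients each) | ICC 0 | ICC 0.01 | ICC 0.02 | ICC 0.05 |
|---|---|---|---|---|
| 5 (30.4) | 80.0% | 74.8% | 69.7% | 56.8% |
| 10 (15.2) | 80.0% | 77.5% | 74.9% | 67.7% |
| 20 (7.6) | 80.0% | 78.8% | 77.6% | 74.1% |
| 30 (5.1) | 80.0% | 79.3% | 78.6% | 76.4% |

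These use normal quantiles. A small-sample correction for few navigators would lower power somewhat further.

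**3. Standard error.** Under the planned rates, the true SE exceeds the independent-patient SE by about 1% to 5% (10 to 20 navigators, ICC 0.01 to 0.02) and by about 24% (5 navigators, ICC 0.05).

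**4. Type I error of the plain chi-square test.** The null here is a zero average effect with navigators that differ around it: 2 × Φ[−1.960 × √(2 / (1 + DE))]. DE = 1.284 gives 6.7%; DE = 2.47 gives 13.7%. Simulation gave 5.4% (20 navigators, ICC 0.01) to 14.0% (5 navigators, ICC 0.05), against 5.3% with no clustering.

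**5. Effect of balancing by center.** With randomization balanced by center, an assumed center ICC of 0.05 and no center term in the test, simulated type I error was 4.5% to 4.6% with no navigator effect, 5.0% with 20 navigators and ICC 0.01, and 13.2% with 5 navigators and ICC 0.05.

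**6. Information on the ICC.** Expected intervention-arm events: 0.125 × 152 = 19, or about 1 to 4 per navigator for 20 down to 5 navigators.

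**The case against.** A reader might infer that the p-value and the power are simply wrong as planned. The documents do not support that.

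- **The size is not known.** No section gives a navigator count, caseload or ICC. At ICC 0 the power is 80.0% for any number of navigators. The largest losses need 5 navigators and ICC 0.05 together. With five centers that could mean one navigator per center, where a navigator effect cannot be told apart from a treatment effect that differs by center. This stands.
- **Type I error need not rise.** Allocation is by patient. If the program affects no patient, sharing a navigator adds no correlation and the chi-square test is valid. Inflation needs navigators whose effects differ around an average of zero. This stands, but that null is relevant when the question is transfer to other navigators.
- **Balancing by center works the other way.** Leaving a balanced factor out of the test makes it slightly conservative and can cancel a small navigator ICC. It does not cancel a large one (step 5).
- **An interval that is too narrow** might also be inferred. The article describes no confidence interval for the primary effect, so nothing can be said about one.
- **The unseen analysis plan may deal with it.** The second-step covariates are unnamed, so a navigator or center term is not excluded. Such a term would still not change the first-step test or the power statement, which this article fixes.
- **The remedy is limited.** With about 19 events the ICC will be estimated poorly. No section lists the navigator as a recorded variable, and the Discussion says that forms are completed anonymously. This is a reason to make the clustered model a sensitivity analysis, not to omit it.

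**Conclusion.** The point holds conditionally. The primary test and the sample size assume independent patients in a design where one arm is clustered by navigator. If navigators differ in effect, 80% power is optimistic: about 75% to 79% for 10 to 20 navigators and ICC 0.01 to 0.02, and about 57% for 5 navigators and ICC 0.05. The p-value is then too small for a claim about the program in the hands of other navigators. As a test of whether the program affects any patient at all, the chi-square p-value stands. The stated 152, 80% and 340 contain no arithmetic error that matters. Navigator numbers, equal caseloads and ICCs are my assumptions, not the protocol's. The change is worth making because it is cheap and bears on the stated purpose of the trial.

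**What to change.** 1. Adjust the primary comparison for center, which is already a randomization factor.
2. Record which navigator served each intervention patient, by a coded identifier that fits the anonymous forms.
3. Pre-specify a sensitivity analysis for hospitalization and for HADS, with navigator as a cluster in the intervention arm only, each control patient as a cluster of one, center as a factor and a small-sample correction. Report the ICC for hospitalization and say that it is imprecise, because only about 19 intervention-arm events are expected.
4. Under Sample size planning, state that 80% power assumes no navigator clustering. Give the number of navigators and the power over a range of ICC and caseload, as in the table above.

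The cost is one extra model per endpoint, keeping a navigator identifier, and a somewhat less favourable stated power. The number of patients and their care stay as they are.
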